#### Interventions

Participants will receive individually tailored treatment determined by their headache specialist in the GPHCM; these include CHM in the form of herbal decoction, granules or patented pill, alone or in combination with western medicine or other treatment procedures such as acupuncture. The treatment plan will be based on discussion between individual participants and their headache specialist, with no limitations or interference set by this study.

#### Recruitment

Recruitment posters have been displayed in the waiting room of the Headache Clinics of GPHCM, and headache specialists received training relating to this study have been given screening forms. Potential participants, who have been pre-screened by the headache specialists for eligibility, will be guided to a private consultation room where the researcher or the independent research assistant will provide a full explanation of the study prior to the process of written informed consent. Refusal of participation will not affect the degree of medical care provided.

#### Data collection

The study will employ a structured CRF (S1 File), which has been specifically designed for this study, including demographic information, symptoms, treatment details, relevant validated questionnaires, participants’ feedback and adverse events (AEs). Face-to-face data collection will be conducted at baseline, while evaluations at other timepoints can be completed using online CRFs or hard copy CRFs, according to participants’ preference. Online data collection will be conducted via the online survey service provider Wenjuan.com (www.wenjuan.com). Participants will be required to take migraine diary and record details of each migraine attack (S2 File). Data of patient-reported MBS, treatments, examinations and diagnostic information will also be extracted from the clinical records by the researcher.

The data to be collected from CRF is outlined below:

*Demographic and general information*. Demographic information including age, gender, general information such as family history, migraine subtypes and other medical histories will be collected upon participant enrolment.

*Patients’ preferences and concerns*. Patients’ preference and concerns regarding CHM treatment for migraine will be collected upon participants’ enrolment.

*Migraine frequency*. Defined as the number of migraine attacks in four weeks. An attack that is interrupted or rescued by sleep or medications but relapses within 48 hours will be considered as one migraine attack; attacks that are separated by an entire 24-hour period will be considered as two distinct attacks [40]. A 50% reduction in migraine frequency within a evaluation interval will be defined as response.

*Migraine days*. Defined as the number of days with migraine headache within each evaluation interval (four weeks) [41].

*Migraine duration*. Defined as the average duration of each migraine attack.

*Pain intensity*. Evaluated via numeric rating scale (NRS), which is an 11-points scale with 0 indicating no pain and 10 indicating the most severe pain. This outcome will provide data regarding the maximal pain intensity prior to taking abortive medication, as well as the average pain intensity across each observational intervals.

*Analgesic consumption*. Data collected under this category include the type, amount and frequency of acute medication, participants’ behaviour when purchasing and using analgesics. The quantity of medications will be standardised using medication quantification scales [42], where available.

*Migraine-Specific Quality of Life Questionnaire version 2*.*1 (MSQ)*. A 14-item patient-reporting outcome instrument that measures the impact of migraine on a patient’s health-related quality of life. The domains cover role function-restrictive, role function-preventive and emotional function [43].

*Generalised Anxiety Disorder 7-item (GAD-7) Scale*. An efficient, practical, patient-reporting scale, which is commonly used for rapid screening and evaluating the presence and severity of anxiety disorder, especially in outpatient settings [44].

*Patient Health Questionnaire-9 (PHQ-9)*. A self-administrative scale to screen, diagnose, monitor and measure the severity of depression [45].

*Insomnia Severity Index (ISI)*. A brief self-reporting instrument measuring the patients’ perception of both nocturnal and diurnal symptoms of insomnia [46, 47].

*Satisfaction of treatment*. Evaluated using 5-point Likert scale [48] at each observational timepoint.

*AEs*. Participants will be asked to report any AEs possibly related to prescribed treatments, analgesics or concomitant medications, such as diarrhea, dental ulcer, insomnia in CRFs at observational visits.

During data collection, the researcher will report patients’ scores of GAD-7, PHQ-9 and relevant AEs to the corresponding clinicians to assist in clinical management.

Migraine diary is a tool for patients to record information of migraine attacks and monitor the frequency, duration, severity, associated symptoms and medication consumption of migraine attacks over time. Data collected from migraine diary will be cross-checked with CRFs as a supplementary method to ensure data accuracy.

Clinical records are referred to collect the following information:

*Treatments*, *examinations and diagnoses*. Treatment prescriptions and courses, results of laboratory and medical imaging examinations, Chinese medicine syndrome diagnosis, and western medical diagnoses will be obtained from clinical records.

*Patient-reported MBS*. Any other symptoms such as dry mouth, constipation, abdominal distention, which have been reported by participants, will be extracted from clinical records.

Fig 1 provides a summary of data collection during each timepoint of this study. Reminders will be sent via Wechat or via mobile phone messaging system to participants prior to each observational timepoint to improve compliance.

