## Methods

### Study design

This prospective, registry-based, observational cohort study is being undertaken at the Headache Clinics at the Guangdong Provincial Hospital of Chinese Medicine (GPHCM) in southern China [38]. Participant recruitment commenced in December 2020 and is targeted to end in May 2022. Based on consecutive sampling, an estimated number of 400 eligible migraineurs will be recruited.

All participants will be required to complete case report forms (CRFs) every four weeks over a period of 12 weeks. Following the same period intervals, data regarding participants’ detailed treatment plan, including medications, administrative methods, courses, dosage and forms of CHM, which have been determined by their headache specialists, will also be collected from their clinical records. Data will be collected for the entire study duration, even in cases where treatments have been discontinued before the end of the observation period.

The study (version 1.0) was approved by the ethics committee of GPHCM (ZE2020-243-01) and registered with the Human Research Ethics Committee of RMIT University (24235). This study complies with the Declaration of Helsinki, Ethical Guidelines for Medical Research on Humans, and Good Clinical Practice guidelines. The protocol has been registered in the Chinese Clinical Trial Registry (No. ChiCTR2000041003). The reporting of this study will abide by the Strengthening the Reporting of Observational Studies in Epidemiology (STROBE) statement for cohort studies [39].

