#### Analytical methods

Data analysis will be conducted in relation to the study objectives:

To summarise participants’ demographic characteristics, preferences and concerns, descriptive analyses will be conducted. Such descriptive analyses will be conducted in subcohorts of patients with various levels of predefined exposures, and compared analysis will be conducted, if appropriate. Categorical variables, including gender and satisfaction degree, will be presented using frequencies and percentages; quantitative variables such as disease duration and migraine frequency will be described with mean values and standard deviation.To display the utilisation pattern of CHM for migraine and to summarise patient-reported MBS, cluster analyses and machine learning algorithms such as Apriori Algorithm [50] will be performed. Apriori Algorithm is a common method to identify core herb pairs and herb combinations [51–53]. Multiple correlation analysis and multivariable regression analysis will be conducted to explore factors related to clinical outcomes, where possible.To evaluate the effects of CHM for adult migraine, generalised estimated equation will be adopted to compare longitudinal differences of clinical outcomes. Disease risk score and instrumental variables will be introduced to control measured and unmeasured confounders, respectively. Missing data will be handled using R-MICE package for the quantitative outcome measures at each evaluation timepoint.

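### Baseline is collected face-to-face and follow-up may be online or on paper, so part of any before-after change on PHQ-9, GAD-7, ISI and MSQ may reflect the change of collection mode

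*Protocol article*

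**What the plan says.** All references are to the Protocol article.

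- Data collection sets one arrangement for baseline against another for follow-up: "Face-to-face data collection will be conducted at baseline, while evaluations at other timepoints can be completed using online CRFs or hard copy CRFs". Which of the two follow-up forms is used is left to the participant.
- Study design gives the schedule: "All participants will be required to complete case report forms (CRFs) every four weeks over a period of 12 weeks".
- Data collection describes PHQ-9 as "A self-administrative scale to screen, diagnose, monitor and measure the severity of depression". MSQ, GAD-7 and ISI are likewise described as reported by the patient.
- Analytical methods states how the effect of CHM is judged: "generalised estimated equation will be adopted to compare longitudinal differences of clinical outcomes".
- Exposures and confounders defines two subcohorts, CHM alone and CHM with conventional prophylaxis. Both receive CHM. Collection mode is not among the measured confounders listed there.
- The limitations paragraph of the Discussion names the absence of a run-in and of randomisation, recall bias and confounding. It does not name a change of collection mode.

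**The concern.** Answers about mood, anxiety, sleep and quality of life can depend on whether a researcher is present. That is plausible here, because the researcher passes PHQ-9 and GAD-7 scores to the treating clinicians (Data collection). If the setting changes between baseline and follow-up, the measured change mixes two things: change under care, and change in how people answer.

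The first objective is to evaluate the effects of CHM, and the evidence for it is change over time. A concurrent group without CHM would show the same mode shift and let it be subtracted, but none is described. The shift could run either way. Under-reporting of distress in front of a researcher at baseline would hide a real improvement; over-reporting would create a false one.

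The safeguards in the plan address other problems. Disease risk scores and instrumental variables deal with confounding of exposure, not with a change in measurement over time. The diary check ("Data collected from migraine diary will be cross-checked with CRFs as a supplementary method to ensure data accuracy") concerns attacks and medication, not these four scales.

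**Working it through.** **No figure to reproduce.** The article states no alpha, power, effect size or SD. The figure of about 400 participants is a forecast from outpatient volume (Estimated number of patients). The check is therefore one of identifiability and bias.

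**Step 1: can the model separate mode from time?** Take 400 participants at T0 to T3, and a mean model with an intercept, indicators for T1, T2 and T3, and an indicator F for face-to-face collection: 5 columns.

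- No follow-up face-to-face: F = 1 − T1 − T2 − T3 in every row. The rank is 4, so F is aliased with baseline versus follow-up.
- 10% or 30% of follow-ups face-to-face (assumed): the rank is 5. The mode effect can be estimated, provided mode is recorded.
- Online versus paper among follow-ups, with time indicators: the rank is 5 in every case tried. This is a different contrast from face-to-face versus remote.

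**Step 2: how much of a shift enters the results?** Let m be the constant difference between face-to-face and remote answers, and p the share of follow-ups done face-to-face.

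- Before-after contrast: bias has size (1 − p) × m. For p = 0 it is 1.0m; for p = 0.3 it is 0.7m.
- Subcohort-by-time contrast: bias has size |pA − pB| × m. With equal shares it is 0; with 10% and 30% it is 0.2m.

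**Step 3: would a small shift show up at this sample size? (illustration, all values assumed)** Take a paired before-after test, two-sided 5%, n = 400, no true change, and correlation rho between the two measurements. In SD units, SE = √(2(1 − rho)/400). For rho = 0.5, SE = √(1/400) = 0.05, so a shift of 0.10 SD gives z = 0.10/0.05 = 2.0 and a rejection probability of 0.52.

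| Assumed mode shift | rho 0.3 | rho 0.5 | rho 0.7 |
|---|---|---|---|
| 0.05 SD | 0.14 | 0.17 | 0.25 |
| 0.10 SD | 0.39 | 0.52 | 0.73 |
| 0.20 SD | 0.92 | 0.98 | >0.99 |

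The table shows only that 400 participants make small shifts detectable. It is not evidence that a shift of any of these sizes exists.

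**The case against.** The strongest reply is that face-to-face describes a setting, not who fills in the form. The article nowhere says that a researcher reads out the questionnaires, and it describes the scales as self-administered or self-reported. If participants complete them on paper in the clinic at baseline and choose paper later, little changes. This stands, and it limits the likely size. It does not remove the point, because the article does not say that baseline works this way, and anyone who moves online still changes form and setting.

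A reader might infer three stronger claims, none of which the text supports:

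- *That every follow-up is remote.* The wording is permissive. It does not say where hard copies are completed, and the adverse-event item speaks of entries "insomnia in CRFs at observational visits". The aliasing in Step 1 holds only if no follow-up is face-to-face.
- *That every before-after comparison is affected.* Most bothersome symptoms do not depend on CRF mode ("Data of patient-reported MBS, treatments, examinations and diagnostic information will also be extracted from the clinical records by the researcher"), and attack data have the diary as a cross-check.
- *That the GEE can never separate mode from effect.* A common shift cancels between subcohorts with the same mode mix, although equality is not assured when participants choose the form.

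It can also be said that the study declares no pre-determined hypotheses and that the Discussion already asks for caution. Both are true, and they make false-positive rates a weak measure of harm. A biased estimate of change still matters for an objective to evaluate effects.

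**Conclusion.** The point holds in a limited form. The plan allows collection setting and mode to differ between baseline and follow-up. For PHQ-9, GAD-7, ISI and MSQ, part of any change from baseline may therefore be a mode effect, and nothing stated in the article guards against it. If no follow-up is face-to-face, the pooled before-after contrast carries the whole shift and cannot be corrected by modelling; with some face-to-face follow-up it carries proportionately less.

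The size and direction of the shift are unknown, and the SD-unit values above are assumptions. The conclusion also takes the shift to be constant over time and across participants. This is a plausible, unquantified bias in an uncontrolled comparison. It is worth fixing because the remedy is cheap, not because harm has been shown.

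**What to change.** 1. In Data collection, state that participants themselves complete PHQ-9, GAD-7, ISI and MSQ at T0, in the online or paper form they will use at T1 to T3. Keep the face-to-face contact for consent, history and checking for blank items.
2. Record the mode at every timepoint.
3. Report a sensitivity analysis of before-after change by mode, for example participants with the same form throughout versus those who switched. Because form is chosen by preference, this is descriptive support, not a clean adjustment. A mode covariate helps only where mode is not fully aliased with time.
4. Flag participants already enrolled under the present procedure.
5. Name the change of mode in the limitations paragraph of the Discussion.

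Change from T1 to T3 avoids the baseline switch but omits the first four weeks, so it is at most supplementary.

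The cost is a few lines of protocol text and one field in the dataset. Both forms exist and the participant is already on site. The small downside is that self-completion at T0 may leave a few more items blank, which the researcher present can check.

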## Objectives

This observational study aims to 1) evaluate the effects and safety of individualised CHM for adult migraine in a real-world setting; 2) identify factors that contribute to clinical outcomes of CHM for migraine; 3) summarise the common patterns of CHM for migraine and its comorbidities; and 4) report on the characteristics of migraine patients who seek CHM management, including their preferences and concerns associated with CHM therapies for their migraine.

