#### Eligibility criteria

Participants will be eligible for registration if they meet the following criteria:

a). diagnosed with migraine according to the ICHD-3 (1); b). first time seeking treatment for migraine in GPHCM; c). able to provide written informed consent; d). aged of 18 years old or above; and e). not concurrently participating in other interventional trials.

Participants will be excluded for registration and participation if they have any of the following conditions: a). diagnosed with diseases which could induce migraine-like headache such as glaucoma, brain tumour, brain injury; b). diagnosis of migraine being corrected to secondary headaches during the observation period; c). severe impairment of speech, vision, memory or cognition that affects communication and ability to complete questionnaires; d). pregnant or breastfeeding; or e). highly dependent on medical care.

Participants will be marked as drop-outs if they request to withdraw from the observation for any reason.

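### The adverse event item asks patients only for events they think may be treatment-related, so all-cause events are under-ascertained for the safety objective

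*Protocol article*

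**What the plan says.** The first objective in the protocol article (Objectives) is to "evaluate the effects and safety of individualised CHM for adult migraine in a real-world setting".

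The AE entry under Data collection belongs to the list of items taken from the case report form (CRF). It states: "Participants will be asked to report any AEs possibly related to prescribed treatments, analgesics or concomitant medications", and continues "such as diarrhea, dental ulcer, insomnia in CRFs at observational visits". After the face-to-face baseline visit, "evaluations at other timepoints can be completed using online CRFs or hard copy CRFs, according to participants’ preference".

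The same section lists what comes from clinical records instead: treatments, diagnoses, "results of laboratory and medical imaging examinations", and any other symptoms that patients mention. Those symptoms are filed as most bothersome symptoms (MBS).

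Eligibility criteria adds a rule that acts after enrolment. Under the lead-in "Participants will be excluded for registration and participation if they have any of the following conditions" it lists "diagnosis of migraine being corrected to secondary headaches during the observation period". Study design states: "Data will be collected for the entire study duration, even in cases where treatments have been discontinued before the end of the observation period". It does not mention re-diagnosed patients.

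**The concern.** Safety data are normally collected whatever the suspected cause, and relatedness is judged afterwards, so that the judgement can be reviewed and revised. Here the judgement comes first and is the patient's. Because follow-up CRFs may be completed online or on paper, no clinician need be present to prompt for events the patient considers irrelevant. An unexpected reaction to a herbal product is the kind of event a patient may not connect with treatment.

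This is a stated collection rule, not a detail left for an analysis plan. If an event was not requested and was not noted elsewhere, no later analysis can recover it. What is at stake is whether the safety half of the first objective can be reported as an AE rate, or only as a rate of events that patients suspected.

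The re-diagnosis rule raises a separate question: whether AEs in patients who were treated and then re-classified remain in the safety summary.

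**Working it through.** The article gives no AE rate, precision target or safety calculation, so there is no figure to reproduce. The check has three parts.

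**1. What each source captures**

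| Source | Content | Relatedness filter | Counted as AE in the article |
|---|---|---|---|
| CRF, AE item | Events the patient thinks possibly related to a treatment or medicine | Yes, by the patient | Yes |
| Clinical records, symptoms | Any other symptom mentioned, e.g. dry mouth, constipation, abdominal distention | No | Not stated; filed as MBS |
| Clinical records, tests and diagnoses | Laboratory, imaging, western and Chinese medicine diagnoses | No | Not stated |

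The examples show the gap. Diarrhoea is given as an AE, while constipation and abdominal distention are given as MBS. A bowel symptom that starts on treatment could sit in the MBS file and never reach the AE count, because no rule links the two.

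**2. Direction and scale of the filter**

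Let N be the number of patients, p the true share with an AE, and f the share of affected patients who link the event to a treatment. The expected number recorded is N × p × f. Since f cannot exceed 1, the recorded count equals or falls below the all-cause count. N = 400 is from the section Estimated number of patients; p and f are assumptions.

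- p = 10%, f = 1: 400 × 0.10 = 40 patients.
- p = 10%, f = 0.9, 0.7, 0.5: 36, 28 and 20 patients.
- p = 1%, f = 1: 4 patients expected; chance of at least one recorded case 1 − 0.99^400 = 98.2%.
- p = 1%, f = 0.5: 2 patients expected; chance 1 − 0.995^400 = 86.5%.

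**3. Does excluding re-diagnosed patients lower the AE rate?**

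Let r be the share re-diagnosed and RR their AE rate relative to the others. The full-cohort rate is (1 − r) × p + r × p × RR; after exclusion it is p. With assumed p = 10% and r = 5%:

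| RR | Full-cohort rate | Rate after exclusion |
|---|---|---|
| 0.5 | 9.75% | 10.0% |
| 1 | 10.0% | 10.0% |
| 2 | 10.5% | 10.0% |
| 3 | 11.0% | 10.0% |

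Numerator and denominator shrink together. The rate can fall, stay the same or rise, so the exclusion is a selection question whose direction is unknown.

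**The case against.** The strongest reply is that the loss may be small. Possible relatedness is a low threshold, and the item covers prescribed treatments, analgesics and concomitant medicines. Losing events that no treatment caused does not understate harm from CHM; only true reactions that the patient does not suspect are lost. This stands as a limit on size. It does not remove the defect, because unsuspected reactions are those that all-cause collection is meant to find.

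Second, the AE item is not the only unfiltered view of the patient. The records supply symptoms, tests and diagnoses, the CRF lists symptoms separately from AEs, and GAD-7, PHQ-9 and ISI record anxiety, depression and insomnia whatever the cause. This stands too. A reader might infer that unsuspected events, including laboratory abnormalities, never enter the data. The article does not support that. What it lacks is a statement that such findings will be counted as AEs.

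Third, the operative wording is in the CRF (S1 File), which is not shown and may be wider. That is a fair limit on certainty. If it is wider, the article describes it wrongly and needs aligning.

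Fourth, recruitment began in December 2020, so changing the question now creates two ascertainment periods. This is a real cost and is taken up under the fix.

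**Conclusion.** The point holds for the AE item. As described, it puts a lay causality judgement ahead of recording, and all-cause AEs are under-ascertained for the safety part of the first objective. The size cannot be derived from the document; the counts above rest on assumed values of p and f. The change is worth making, but the point falls short of a defect that must be fixed before the study can be relied on.

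Four stronger readings are tempting and are not supported:

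- **That the re-diagnosis rule under-counts AEs.** Eligibility criteria does not say that AE data already collected are discarded, and part 3 of the check shows that removal need not lower the rate.
- **That re-diagnosed patients are mostly those not improving.** Nothing in the article says so.
- **That the filter biases a safety comparison of the subcohorts.** Both subcohorts take CHM, no subcohort safety comparison is specified, and unequal suspicion of herbal and conventional products would be an assumption.
- **That a zero-event bound must be inflated by a set factor.** With 0 of 400 the one-sided 95% upper bound is 1 − 0.05^(1/400) = 0.75%. Dividing by assumed reporting fractions of 0.5 or 0.25 gives 1.5% or 3.0%. The article makes no zero-event claim and gives no reporting fraction, so these bounds are not evidence.

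**What to change.** 1. Ask in each follow-up CRF for any new or worsened symptom, illness or hospital visit since the last CRF, whatever the suspected cause.
2. Record relatedness afterwards, in a separate field, and state who assigns it.
3. Add a field to the record extraction so that treatment-emergent symptoms, diagnoses and abnormal results count as AEs as well as MBS or examinations.
4. Report all-cause and related events separately.
5. State that AEs of treated participants later re-diagnosed with secondary headache stay in the safety summary, to avoid selection on post-baseline information.
6. If S1 File already asks the wider question, correct the AE entry under Data collection to match it.

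The cost is one reworded question, a relatedness field and one extraction field on records already being read. The downsides are more unrelated events to code and a change of question part-way through. Participants already followed answered the narrower item, so AE results should be shown by question version. For those participants, the clinical records can still recover some events.

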**Methods and analysis:**

The study is being undertaken at the Guangdong Provincial Hospital of Chinese Medicine (GPHCM) from December 2020 to May 2022. We anticipate that approximately 400 adult migraineurs will be enrolled and observed on their migraine severity, analgesic consumption, quality of life, anxiety, depression and insomnia at baseline and then every four weeks over 12 weeks. Treatments, diagnostic information, and patient-reported most bothersome symptoms will be collected from patient clinical records. Patient’s demographic data, preferences and concerns on CHM treatments will also be gathered at baseline and be analysed. Factors related to clinical outcomes will be explored with multiple correlation and multivariable regression analyses. Effects of CHM will be evaluated using generalised estimated equation, based on clinical outcome data.

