#### Exposures and confounders

In this real-world observational study, CHM treatment is defined as the main exposure. Participants being treated with CHM solely and those treated with a combination of conventional prophylactic treatment and CHM will be considered as two subcohorts for analyses.

Measured confounders in this study include comorbidities of migraine (depression, anxiety and insomnia, evaluated by PHQ-9, GAD-7, and ISI, respectively), gender, baseline severity of migraine (duration, average frequency, average pain NRS and analgesics consumption at entrance), association with the menstrual cycle (pure menstrual migraine vs menstrually related migraine vs non-menstrual migraine), and aura (migraine with aura vs migraine without aura).

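### Symptoms in the clinical record are classed as MBS with no onset rule or stated route into the adverse event data, so new complaints on CHM can be missed or counted twice.

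*Protocol article*

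**What the plan says.** The Data collection section of the protocol article describes two routes by which a symptom can enter the dataset.

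- **Adverse events, from the CRF.** "Participants will be asked to report any AEs possibly related to prescribed treatments, analgesics or concomitant medications". The examples and the source follow: "such as diarrhea, dental ulcer, insomnia in CRFs at observational visits".
- **MBS, from the clinical record.** "Data of patient-reported MBS, treatments, examinations and diagnostic information will also be extracted from the clinical records by the researcher". The MBS item itself reads: "Any other symptoms such as dry mouth, constipation, abdominal distention, which have been reported by participants, will be extracted from clinical records".

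Insomnia, one of the adverse event examples, has two other roles. It is a repeated outcome (abstract, Methods and analysis: "quality of life, anxiety, depression and insomnia at baseline and then every four weeks over 12 weeks"). It is also a measured confounder (Exposures and confounders: "comorbidities of migraine (depression, anxiety and insomnia, evaluated by PHQ-9, GAD-7, and ISI, respectively").

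Safety belongs to the first objective. Analytical methods puts MBS into the cluster and Apriori work, in the same sentence as the pattern of CHM use. The Discussion presents MBS as a clinical assessment alongside the usual migraine outcomes.

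**The concern.** In a cohort without randomisation or a run-in period, onset relative to the first prescription is the basic information that separates a presenting complaint from a possible harm. Neither definition uses it. The MBS item accepts every other symptom in the record, and its examples are mouth and bowel complaints. Two of the three adverse event examples are also mouth or bowel complaints, so a new complaint of this kind on treatment could plausibly belong to either class.

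Two results are at stake. The safety results may omit complaints that arose on treatment. The MBS patterns may present such complaints as part of the clinical picture for which CHM was prescribed.

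**Working it through.** The article states no adverse event or MBS rate, so there is no figure to reproduce. The check sets the definitions side by side.

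**Step 1: criteria.** The adverse event item has one criterion, possible relation to a treatment or medication, and the participant is the one who reports it. It has no timing or worsening test. The MBS item has no criterion beyond the symptom having been reported and being in the record.

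**Step 2: time window.** The MBS item is not limited to the index visit. Study design says that data are collected for the whole study period, that is 12 weeks, even if treatment stops, and that treatment details are taken from the records at four-week intervals. Post-baseline notes are thus within reach of the MBS definition.

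**Step 3: links between the routes.** The items listed for extraction from the record are treatments, examinations, diagnoses and MBS. Adverse events are not among them. The migraine diary is cross-checked against the CRF, but it covers migraine attacks. The researcher passes relevant adverse events to the clinicians, which runs from the study to the clinic and not back. No described step carries a new complaint from the notes into the adverse event data.

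**Step 4: apply the definitions to four cases.**

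1. Present before CHM and told to the clinician at the index visit: MBS. Correct.
2. Begins on CHM and reported only in the CRF as possibly related: adverse event. Correct.
3. Begins or worsens on CHM, told to the clinician, not reported in the CRF: MBS only. Missing from the safety results.
4. Begins or worsens on CHM, told to the clinician and reported in the CRF: both. The adverse event is captured, but the same complaint also counts as MBS.

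Cases 3 and 4 are the fault. Case 3 lowers the adverse event count. Case 4 leaves that count unchanged but adds a possible harm to the MBS patterns.

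**Step 5: size.** Participants affected by case 3 = 400 × (proportion with a new or worsened complaint noted in the record) × (proportion of those who do not report it in the CRF). The document gives neither proportion. All that follows from its own numbers is the scale: 400 × 1% = 4 participants for each percentage point of that product.

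**The case against.** The strongest reply has four parts.

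- **Sorting is not purely by source.** The adverse event item asks for possible relatedness, which is a substantive filter. This stands. But it is the participant's attribution and not a timing test, and it does nothing for complaints that reach only the clinician.
- **The routes are not exclusive.** The CRF asks about adverse events whatever the clinician writes, and the two lists of examples share no item. This also stands. A reader might infer that symptoms arising on treatment are moved out of the safety results by rule. The article has no such rule: loss is possible, and so is double entry.
- **Insomnia can be checked.** A reader might infer that pre-existing insomnia will be counted as harm. The text does not support this. Participants are asked for possibly related events, not for any insomnia; ISI is taken at baseline and at follow-up; and "migraine subtypes and other medical histories will be collected upon participant enrolment". What remains is only that the article does not link an insomnia event to the change in ISI.
- **Forms are not shown.** The CRF (S1 File) and the schedule in Fig 1 are not available, and either may hold an onset date or a baseline symptom list. So it cannot be said that onset is recorded nowhere. An onset date in the CRF would serve events reported there; MBS come from the clinical record.

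It could also be said that classification rules belong in the analysis plan. Here, however, the broad class is fixed in the data collection text, and an analysis plan cannot reliably recover onset that was not captured at extraction.

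**Conclusion.** The concern holds in a limited form. As written, the MBS and adverse event definitions overlap, neither separates symptoms that began or worsened on treatment, and no described route takes a new complaint from the record to adverse event assessment. Such a complaint can be counted as MBS and be missing from the safety results, or be counted in both.

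This rests on two assumptions: that MBS extraction covers post-baseline notes, which the text allows and nowhere restricts, and that some complaints reach the clinician but not the CRF. The size is unknown. It would be tempting to conclude that the safety and MBS results are biased in opposite directions, or to attach a case count. The article supports neither, because it gives no rates and the insomnia part is weak. The correction is still worth making, because it is cheap and bears on a stated objective.

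**What to change.** At record extraction, flag each symptom as present before the first CHM prescription, new, worsened or unknown. Base the flag on reported onset and not on first mention: a long-standing symptom first mentioned at week 4 is not a new event. Then:

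- send every new or worsened symptom to adverse event assessment, whatever its source, and remove duplicates against the CRF;
- report MBS patterns separately for symptoms present at T0 and for those arising later, so that later symptoms are kept and not mistaken for presenting complaints;
- report insomnia adverse events alongside the ISI change from T0, without using ISI as a gate. A gate could pass a one-point fluctuation as confirmation, or discard an event that the participant attributes to treatment when the total has not risen.

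The cost is one extra field in an extraction already planned and a sentence or two in the protocol. The reported adverse event count will probably rise, and some onsets will stay unknown where the notes do not state them.
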